### Confidentiality

The Chief Investigator will preserve the confidentiality of participants taking part in the study and is registered under the Data Protection Act.

### Indemnity

Singapore General Hospital, Singapore holds negligent harm and non-negligent harm insurance policies which apply to this study. Patients attending Roscommon University Hospital, Ireland for their care will be eligible for compensation for negligent or non-negligent harm via the Clinical Indemnity Scheme.

## Discussion

The role of compression following endovenous interventions for superficial venous reflux remains unclear. If indicated, the optimal duration of treatment is also obscure. Non-tumescent, non-thermal (NTNT) endovenous techniques are increasingly used as they facilitate a more office-based approach to venous interventions. The COMMOCA trial will provide valuable data regarding the role of compression as an adjunct to one of the NTNT techniques. The primary aim of the study is to assess patient’s pain scores for the first 10 days post procedure using a visual analogue scale. Secondary aims include an assessment of patient compliance with compression, quality of life scores, clinical effectiveness, rates of bruising and phlebitis, time taken to return to normal activities, patient satisfaction and occlusion rate at 6 months.

This trial has some potential weaknesses, including the simple randomisation technique which has been chosen. This may lead to issues such as the production of unequal sample sizes. Additionally, the potential for losses to follow-up is a weakness in any trial of venous interventions. Short-term outcomes such as pain score are relatively straightforward to capture. However, early recurrence and recanalisation rates are of major concern to interventionists and require longer follow-up. COMMOCA is set in two established ambulatory venous centres with pathways for follow-up already in place. Between them, the two centres undertake over 1000 superficial venous procedures per annum. Six-month follow-up completion rates will be monitored closely throughout the trial. If necessary, the sample size will be recalculated to reflect a greater than expected drop-out rate and ensure sufficient statistical power regarding recanalisation rates at the end of the trial.

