### Study setting

The trial will take place in Singapore General Hospital, Singapore and Roscommon University Hospital, Ireland.

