### Description of intervention

Patients will be randomised (using computer-generated random numbers in sequentially numbered, opaque, sealed envelopes) to have compression (group A) or no compression (group B). The compression therapy used will be Class II (18–24 mmHg) above-knee compression stockings. Patients randomised to group A will be asked to wear compression stockings for 1 week. This would involve wearing the stocking during the daytime but patients will be allowed to take it off at night whilst in bed. Patients randomised to group B will not be provided with any compression. Those requiring concurrent phlebectomies will be excluded. Patients allocated to compression will all wear the same length, style and grade of stockings.

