### Sample size and study duration

The sample size needed to observe a difference of at least 20 mm in the VAS score with a standard deviation of 20 mm was estimated. With power of 90% and 5% significance equivalence, a minimum of 94 patients (47 per group) will need to be recruited. Accounting for losses to follow-up in the order of 10% gives a target sample size of 103 patients.

Previous studies looking at compression stockings have shown high drop-out rates close to 40% at 3 months. We do not anticipate this problem with the set up in the outpatient clinic at Changi General Hospital in Singapore. If we estimate 10% drop-out, this would mean we would need near to 200 patients to be included in this study. If three patients are recruited per week, this would take approximately 17 months to recruit the necessary number of patients. With 6 months follow-up, therefore, the study will be running for 23 months, but 3 years would give a good safety net for recruitment and follow-up, and allow for dropouts. We aim to have recruited 100 patients within the first 12 months of the study.

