## Trial status

Study Protocol Version 1.4 dated 29 January 2018. Recruitment has not yet commenced.

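### Simple randomisation across two countries is valid, but per-site lists with concealed, varying blocks and a pain comparison that accounts for site would be a cheap improvement before recruitment

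*Protocol article*

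**What the plan says.** The Description of intervention section gives the allocation method as "using computer-generated random numbers in sequentially numbered, opaque, sealed envelopes" and mentions neither blocks nor strata. The Discussion names the method and its drawback: "This trial has some potential weaknesses, including the simple randomisation technique which has been chosen", followed by "This may lead to issues such as the production of unequal sample sizes". Unequal arm sizes are the only consequence it names; balance between sites is not discussed.

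On sites, Study setting states: "The trial will take place in Singapore General Hospital, Singapore and Roscommon University Hospital, Ireland". The primary outcome is a pain score that patients record daily on a visual analogue scale for 10 days (Aims; Baseline). Statistical analysis compares pain scores by the Mann–Whitney *U* test. It also plans a regression for predictors of higher pain, without listing covariates. The only blinding it states is that of the analyst.

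The sample size rests on "a difference of at least 20 mm in the VAS score with a standard deviation of 20 mm" and concludes: "With power of 90% and 5% significance equivalence, a minimum of 94 patients (47 per group) will need to be recruited". That is raised to 103 for 10% loss. The next paragraph, also at 10% loss, gives a total of about 200. Trial status says: "Recruitment has not yet commenced".

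**The concern.** Unrestricted randomisation leaves two things to chance: the sizes of the arms, and the mix of Singapore and Irish patients within each arm. The second matters more here. Pain is subjective, patients know whether they were given stockings, and any difference between the sites in pain reporting or procedural practice would carry over into the arm comparison to the extent that the site mix differs. A Mann–Whitney test without strata cannot remove that. What is at stake is precision and the credibility of the comparison, in a trial whose allocation list could still be changed when the article was written.

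**Working it through.** **1. The plan's own sample size.** Inputs from Sample size and study duration: difference δ = 20 mm, SD σ = 20 mm, power 90%, two-sided 5% (sidedness assumed). The per-group size is n = 2(1.960 + 1.282)²(σ/δ)² = 2 × 10.51 × 1 = 21.01, rounded up to 22, or 44 in total. The stated 47 per group does not follow from these inputs; it would need an SD of about 29.9 mm. That is a separate matter, but it affects how the loss of power is judged, so both SDs are used in step 3. The step to 103 does reproduce: 94 × 1.1 = 103.4.

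**2. Arm sizes under simple 1:1 randomisation.** The number in arm A is Binomial(N, 0.5), so the difference in arm sizes has SD √N.

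- N = 103: SD = √103 = 10.1 patients. P(arms differ by 11 or more, i.e. 57:46 or worse) = 0.324. P(60:40 or worse) = 0.048.
- N = 200: P(55:45 or worse) = 0.18. P(60:40 or worse) = 0.006.

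**3. What unequal arms cost.** With arm sizes a and N − a, efficiency relative to equal arms is 4a(N − a)/N², with mean 1 − 1/N. For N = 103 that is 1 − 1/103 = 0.990, a loss of about 1%. For N = 200 it is 0.995.

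Power is Φ(δ / (σ√(1/n₁ + 1/n₂)) − 1.96), by normal approximation:

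| Arms (94 patients) | SD 20 mm (stated) | SD 29.9 mm (94 gives 90%) |
|---|---|---|
| 47/47 | 99.8% | 90.0% |
| 57/37 | 99.7% | 88.7% |
| Average under simple randomisation | 99.8% | 89.7% |
| 50/44 (worst case, two sites, blocks of at most 6) | 99.8% | 89.9% |

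The last row follows because blocks of 4 or 6 (assumed sizes) can leave an excess of at most 3 per site, so 6 over two sites.

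**4. Balance of sites between arms.** The article does not give the split of patients between sites, so the smaller site's share is assumed. The probability that this share differs by 10 percentage points or more between arms was simulated with 200,000 runs per cell:

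| Smaller site's share (assumed) | N = 103 | N = 200 |
|---|---|---|
| 10% | 0.09 | 0.02 |
| 20% | 0.22 | 0.08 |
| 30% | 0.27 | 0.12 |
| 50% | 0.33 | 0.18 |

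With blocks stratified by site these probabilities are close to zero.

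**5. What site imbalance does to the result.** The shift in the arm difference is the difference in site share times the difference in pain between sites. With an assumed 10 mm difference between sites, a 10-point imbalance moves the contrast by 0.10 × 10 = 1 mm. One SD of chance imbalance at N = 103 (0.059 to 0.100 across the assumed shares) moves it by 0.6 to 1.0 mm, against the 20 mm the trial is designed to detect.

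**The case against.** The strongest reply is that simple randomisation is valid, unbiased and the least predictable method, and that the authors disclosed its drawback. All of that stands. So does the small size of the harm: at most 1.4 power points at 57/37 even if 94 patients gave exactly 90% power, and about 1 mm for a site difference that is itself assumed. If the total is about 200, the imbalance is smaller still. What remains is that the choice is stated, it is conceded to be weak, and a better list could be had for little.

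A reader might infer more than the article supports:

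- **Exclusions after randomisation.** The Description of intervention says "Those requiring concurrent phlebectomies will be excluded" just after describing allocation, which could suggest patients being removed once their envelope is open. The Enrolment criteria, however, already exclude patients who need adjuvant vein treatment, so this reads as an eligibility rule. The article is silent on when envelopes are opened, and a condensed article commonly leaves that to the full protocol.
- **Operator knowledge.** The same silence means that the article does not show the operator to be aware of the allocation during the procedure.
- **No adjustment for site anywhere.** The stated primary comparison is unadjusted, but the covariates of the planned regression are not listed and may be set elsewhere.
- **A free and complete cure.** Blocking bounds imbalance but does not abolish it, and it makes some allocations easier to guess.

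**Conclusion.** This is a worthwhile low-cost improvement. It is not an error, and it does not threaten the primary result. The expected loss is about 1% of efficiency. The better argument is site balance: a 9% to 33% chance at 103 patients, or 2% to 18% at 200, of a 10-point or larger difference in site share. These figures rest on an assumed smaller-site share of 10% to 50%, and the effect in millimetres on an assumed 10 mm difference between sites. That site strata are absent follows from the authors' description of the method as simple; that patients know their allocation follows from comparing stockings with none. The article says neither in so many words.

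**What to change.** Before the first patient is randomised, replace the single unrestricted list with one list per site, using permuted blocks whose sizes vary at random and are concealed from those who recruit. Make the primary pain comparison account for site, for example by a site-stratified Wilcoxon (van Elteren) test, which stays closest to the planned Mann–Whitney test, or by a regression with a site term. State the site list unambiguously first: Sample size and study duration refers to an outpatient clinic at a Singapore hospital that Study setting does not list. Reconcile the totals of 103 and about 200 so that the lists have the right length.

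The costs are re-issued envelopes, an update to the protocol and analysis text, and a small change to the stated primary test. The statistical downside is that staff who can see past allocations may guess some later ones; varying and concealing the block sizes limits this.

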## Methods

### Aims

The primary aim of the study is to assess patient’s pain scores for the first 10 days post procedure using a visual analogue scale (VAS). Secondary aims are to compare the two treatment groups with respect to: quality of life scores at baseline, 2 weeks and 6 months using the EQ-5D (EuroQol 5 Dimensions), AVVQ (Aberdeen Varicose Vein Questionnaire) and CIVIQ (ChronIc Venous Insufficiency quality of life Questionnaire) scores; clinical change using the VCSS (Venous Clinical Severity Score) at baseline, 2 weeks and 6 months; the degree of bruising (mild, moderate and severe) and phlebitis at 2 weeks and 6 months; patient compliance with the intervention; time taken to return to work and normal activities; patient satisfaction, assessed with a patient satisfaction questionnaire; and successful obliteration of the target vein, assessed with duplex ultrasound scan at 6 weeks and 6 months. Recanalisation will be defined by a segment of vein ≥ 5 cm. A comparison of the cost-effectiveness of the intervention will also be carried out.

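### A recalculation for drop-out cannot ensure power for recanalisation, because the only sizing shown is for pain and no recanalisation rate, difference or power is given

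*Protocol article*

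**What the plan says.** The statement is in the Protocol article, Discussion, in the paragraph on weaknesses. After noting that recanalisation needs longer follow-up and that 6-month completion will be monitored, the article says that, if needed, "the sample size will be recalculated to reflect a greater than expected drop-out rate and ensure sufficient statistical power regarding recanalisation rates". The trigger is drop-out above expectation and the stated result is power for recanalisation.

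The sizing is in Methods, Sample size and study duration. It concerns pain: "The sample size needed to observe a difference of at least 20 mm in the VAS score", with a standard deviation of 20 mm. It continues "With power of 90% and 5% significance equivalence", and concludes that "a minimum of 94 patients (47 per group) will need to be recruited". Two enrolment targets follow, both at 10% loss: "Accounting for losses to follow-up in the order of 10% gives a target sample size of 103 patients", and then "this would mean we would need near to 200 patients to be included in this study".

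Methods, Aims makes pain over the first 10 days primary and obliteration of the target vein secondary. It defines the event ("Recanalisation will be defined by a segment of vein ≥ 5 cm") but gives no expected frequency. Methods, Statistical analysis assigns categorical outcomes to the chi-square or Fisher's exact test.

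**The concern.** The Discussion treats power for recanalisation as something the design has, that excess drop-out could erode, and that recalculation would restore. Nothing in the article establishes that power, even with complete follow-up. A recalculation needs a target to recalculate towards, and for recanalisation there is none.

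The trigger also fits the sizing endpoint poorly. The number of patients rests on a 10-day diary collected at the 2-week visit, whereas the Discussion monitors completion at 6 months. Patients lost after the 2-week visit reduce the recanalisation data but not the pain data.

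At stake is how the 6-month occlusion comparison is understood. The article itself describes recanalisation as a major concern for those who treat veins. A reader who accepts the Discussion would give a null comparison more weight than the numbers can bear.

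**Working it through.** **1. The plan's own figure.** Inputs from Sample size and study duration: difference 20 mm, SD 20 mm, power 90%, significance 5% (two-sided assumed).

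n per group = 2 × (1.960 + 1.282)² × (20/20)² = 21.0, so 22 per group or 44 in total.

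The stated 47 per group is not reproduced. A t-test version gives 23, a Mann–Whitney adjustment 24 to 26, and an equivalence reading with a 20 mm margin 22 to 26. At 47 per group the stated pain inputs have 99.8% power. The 103 is 94 × 1.1 = 103.4. These are separate matters, but they matter here in one respect: no reading of the pain inputs brings recanalisation into the calculation.

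**2. Power for recanalisation.** The article gives no rates, so every pair below is assumed. Two-sided 5%, n per arm, p̄ the mean of p1 and p2:

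power = Φ{ [ |p1 − p2|√n − 1.96√(2p̄(1 − p̄)) ] / √(p1(1 − p1) + p2(1 − p2)) }

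Example, 10% vs 20% at n = 47: (0.100 × 6.856 − 1.96 × 0.505) / 0.500 = (0.686 − 0.990) / 0.500 = −0.608, and Φ(−0.608) = 27.1%.

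The columns are 42 per arm (47 less about 10%), 47 per arm (the stated minimum), 100 per arm (the target of about 200 with no losses), and the evaluable number per arm for 80% power.

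| Assumed rates | n = 42 | n = 47 | n = 100 | n per arm for 80% |
|---|---|---|---|---|
| 10% vs 15% | 10.2% | 10.9% | 18.6% | 686 |
| 5% vs 10% | 13.7% | 14.8% | 26.7% | 435 |
| 15% vs 25% | 20.6% | 22.5% | 42.3% | 250 |
| 10% vs 20% | 24.7% | 27.1% | 50.8% | 199 |
| 5% vs 15% | 33.0% | 36.4% | 65.6% | 141 |
| 15% vs 30% | 37.5% | 41.2% | 72.2% | 121 |
| 10% vs 25% | 43.9% | 48.1% | 80.2% | 100 |
| 5% vs 20% | 54.8% | 59.7% | 90.0% | 76 |
| 5% vs 25% | 73.6% | 78.4% | 98.1% | 49 |

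At 51 per arm (the target of 103 with no losses), the first and last rows become 11.5% and 81.7%.

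**3. Sensitivity to the test.** Exact enumeration at 47 per arm gives, for Fisher's test and the uncorrected chi-square test respectively:
- 5% vs 10%: 6% and 17%
- 5% vs 15%: 22% and 40%
- 10% vs 20%: 18% and 29%
- 5% vs 25%: 71% and 83%

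The choice of test moves the figures by several points or more, but does not change the picture for differences of 5 to 10 points.

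**4. What correcting for drop-out can do.** Going from 47 to 42 evaluable per arm lowers power for 10% vs 20% only from 27.1% to 24.7%. Replacing every lost patient returns it to 27.1%. Drop-out is not what limits power for this endpoint.

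**5. Precision.** With the same rate p in both arms and 47 per arm, the 95% confidence interval half-width for the risk difference is 1.96 × √(2p(1 − p)/47): 8.8 points at 5%, 12.1 at 10% and 14.4 at 15%.

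**The case against.** The strongest reply has several parts.

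- **The rates are not the article's.** This stands. A reader might take one narrow range of power, such as 15% to 36%, as a property of the trial. It holds only for 5% vs 10% and 5% vs 15%, and nothing in the text makes those differences more likely than others.
- **The trial may enrol more than 94.** This stands in part. The article also gives 103 and about 200, and at the larger number some differences of 15 points or more do reach 80%. Smaller ones in the table do not.
- **The statement is conditional and sits among the weaknesses.** True, so it is not an unqualified promise. But the condition concerns whether to recalculate. The result claimed for the recalculation is still power for recanalisation.
- **The article condenses a fuller protocol.** A recanalisation target might exist there, and the larger enrolment figure has no derivation shown. So one can say that no sizing for recanalisation is shown, not that none was ever done. The point rests on what the article asserts and not on an omission.
- **Six-month losses are not wholly separate from the diary.** Also true: patients lost before the 2-week visit are missing for both outcomes.

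Two stronger inferences are tempting and lack support. One is that a non-significant occlusion result will be presented as proof that closure is unaffected. The article plans only a test and says nothing about reading p > 0.05 as equality. The other is that the recalculation would enlarge the trial several-fold. A drop-out adjustment would not do that, and no power target is stated that would.

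**Conclusion.** The concern holds in a limited form. The Discussion attributes to a drop-out-driven recalculation a result it cannot deliver: it can at best restore a number derived from pain, and that number carries no stated power for recanalisation.

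Under the assumed rates in the table, and by the normal approximation, power at 47 per arm is about 11% to 78% for differences of 5 to 20 points. At 100 per arm with no losses it is 27% for 5% vs 10%, 51% for 10% vs 20% and 66% for 5% vs 15%. Among the pairs tried it reaches 80% only from about 15 points, and not for all of those (15% vs 30% gives 72%). The size therefore depends on unstated rates, on which enrolment target applies and on the test used. The logical fault depends on none of these. The primary pain comparison is unaffected.

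**What to change.** - Remove the statement that recalculation will ensure power for recanalisation, and state that the trial is sized for pain.
- Base any drop-out-driven recalculation on the proportion of patients with a usable primary pain diary.
- Report 6-month occlusion as a risk difference with a 95% confidence interval. State the expected precision (half-width about 9 to 14 points at 47 per arm for assumed rates of 5% to 15%), and say that equal closure will not be inferred from p > 0.05.
- If the sponsor prefers to keep a power aim for recanalisation, state the expected rate, the target difference and the power that the recalculation will use, and accept the enrolment that follows.

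The first three changes are rewording and need no extra patients. The article reports that recruitment had not begun. The cost is that the stated property of the trial becomes less favourable. Only the last option could raise enrolment, for example to 199 evaluable per arm for 80% power at an assumed 10% vs 20%.

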## Trial status

Study Protocol Version 1.4 dated 29 January 2018. Recruitment has not yet commenced.

## Data Availability

The datasets generated and/or analysed during the current study are not publicly available as recruitment has not yet commenced, but final data will be available from the corresponding author on reasonable request following study completion.

## Abbreviations

ABPI: Ankle–Brachial Pressure Index
AE: Adverse event
AVVQ: Aberdeen Varicose Vein Questionnaire
CEAP: Clinical–Etiological–Anatomical–Pathophysiology
CIVIQ: ChronIc Venous Insufficiency quality of life Questionnaire
COMMOCA: COMpression Therapy Following MechanO-Chemical Ablation
CVD: Chronic venous disease
EQ-5D: EuroQol 5 Dimensions (standardised instrument for use as a measure of health outcome)
EVLT: Endovenous laser therapy
GSV: Great saphenous vein
IUP: International Union of Phlebology
MOCA: Mechano-chemical ablation
NICE: National Institute for Clinical Excellence
NRES: National Research Ethics Service
RFA: Radiofrequency ablation
SAE: Serious adverse event
SPIRIT: Standard Protocol Items: Recommendations for Interval Trials
SSV: Short saphenous vein
STS: Sodium tetradecyl sulphate
VAS: Visual analogue scale
VCSS: Venous clinical severity score
